#### *Data collection*

After we have received informed consent from the parents, blood samples 0.9 ml from the child will be taken according to present clinical practice at if possible from cord (2ml) and at days 0, 7, 14, 28 and in postmenstrual weeks 32, 36 and 40. Blood samples from the mothers for FA analyses will be taken after birth, day 7 and at gestational weeks 36 and 40. At the same time (except from day 1), breast milk samples are taken. Length, weight and head circumference are measured weekly.

Screening for ROP will be performed, at least once a week, according to clinical routines using a specific protocol.

We intend to analyze the content of phospholipids which can be done on small amounts of blood, is relatively insensitive to short term fluctuations in intake and mirror the composition of many membranes in the body. The analyses will be made using gas-liquid chromatography. The method has a coefficient of variability of 1-3% for the FAs concerned.

| Study Day ==>                                                                     | 0
(Birth) | Week
1 | Week 2 | 28 GW | 32 GW | 36 GW | 40 GW |  |  |
|-----------------------------------------------------------------------------------|--------------|-----------|--------|-------|-------|-------|-------|--|--|
| Examination / Sampling                                                     |              |           |        |       |       |       |       |  |  |
| Informed Consent                                                           | X            |           |        |       |       |       |       |  |  |
| Maternal- & perinatal medical history                                  | X            |           |        |       |       |       |       |  |  |
| Physical Exam/Apgar Score                                                  | X            |           |        |       |       |       |       |  |  |
| Vital signs (Heart rate, blood pressure, pO2, breath frequency) |              |           |        |       |       |       |       |  |  |
| Weight, length, HC                                                         | X            | X         | X      | X     | X     | X     | X     |  |  |
| Adverse Events                                                             | X            | X         | X      | X     | X     | X     | X     |  |  |
| Cranial/cerebral US                                                        | X            | X         | X      | X     | X     | X     | X     |  |  |
| Fatty acid sampling- serum (child)                                         |              |           | X      |       |       |       |       |  |  |
| Fatty acid sampling-breast milk (mother)                                   | X            | X         | X      | X     | X     | X     | X     |  |  |
| Chemistry and Hematology                                                   |              | X         | X      | X     | X     | X     | X     |  |  |
| Study Enrollment                                                           | X            | X         | X      | X     | X     | X     | X     |  |  |
| Parenteral SMOFlipid®/ Clinoleic                               | X            |           |        |       |       |       |       |  |  |
| MRI of the brain                                                           | X            | X         | X      |       |       |       |       |  |  |
| Clinical examination                                                       |              |           |        |       |       |       | X     |  |  |
| Neurological and cognitive examination                                     |              |           |        |       |       |       |       |  |  |
| Ophthalmological examination                                   |              |           |        |       |       |       |       |  |  |
|                                                                                   |              |           |        |       |       |       |       |  |  |
|                                                                                   |              |           |        |       |       |       |       |  |  |

Table 1: Study events

 The time-period of parenteral nutrition will be according to clinical routines, varying from 1 day to maximum age 36 weeks PMA.

 Screening examinations for ROP will be performed weekly from five-six weeks after birth

## **5 STUDY SUBJECTS**

### **5.1 Number of Subjects**

For efficacy evaluations, 80 subjects need to be included for statistical considerations. However, to compensate for protocol violations and withdrawals up to 90 subjects will be included (see **11.1 De-termination of Sample Size and Statistical Methods** on page 26).

After the first 20 subjects have been treated and evaluated there will be a safety check to confirm that the safety profile is acceptable and that the assumption of a 50% reduction in ROP incidence is reasonable. A second safety check will be performed after the next 20 subjects.

### **5.2 Inclusion Criteria**

Subjects must meet all the following inclusion criteria to be permitted into this study:

1. Signed informed consent from parents/guardians;
2. Subject must be below 28 weeks of gestation

### **5.3 Exclusion Criteria**

Subjects presenting with any of the following will be excluded from the study:

1. Detectable clinical gross malformation;
2. Known or suspected chromosomal abnormality, genetic disorder, or syndrome, according to the investigator's opinion;
3. Fish allergy or other severe allergy in the mother
4. Clinically significant neuropathy, nephropathy, retinopathy, or other micro- or macrovascular disease requiring treatment, according to the investigator's opinion;
5. Any other condition or therapy that, in the investigator's opinion, may pose a risk to the subject or interfere with the subject's ability to be compliant with this protocol or interfere with interpretation of results.
6. Bleeding disorder.

## **6 STUDY TREATMENT**

### **6.1 Investigational Product**

Fresenius-Kabi AB has received marketing authorization for SMOFlipid® for parenteral nutrition.

Fresenius Kabi will supply SMOFlipid® for the study. The pharmacy at the study site will be responsible for storing and dispensing all supplies.

The formulation must be stored at +4 to +6.

### **6.2 Study Drug Administration and Dosing**

Regarding fatty acid supplementation to preterm infants the today's regime at all neonatal intensive care units in Sweden is to prepare a mixture of Vitalipid infant and Soluvit with Clinoleic. In addition, according to today's clinical praxis and pharmacy regimes the preparation of Clinoleic, Vitalipid infant and Soluvit lasts for seven days if stored at +4 to +6 and prepared by the local pharmacy.

#### **Preterm Child – Treated**

All infants will receive parenteral and enteral nutrition according to clinical practice and routines.

The group of infants randomized to treatment with Omega-3 will receive SMOFlipid® (with Vitalipid infant and Soluvit supplementation) with a quotient between Omega 6 and Omega 3 that is 2.5:1. The time period for the parenteral nutrition will be according to the need of each infant and clinical practice.

There may be clinical situations when the infant do not tolerate any enteral feeding at all for a period leading to an increased dose of fat till at most 3 g/kg/ for a 1 kg infant over 24 hours. It is extremely rare in our neonatal intensive care unit that a WLBW infant is planned to receive more than 2 g fat/kg/24 h intravenously, but if it should happen the infant is always very thoroughly followed by clinical checkups, daily measurements of plasma triglycerides and blood gases.

#### **Preterm Child - Conventional fatty acid supplementation**

A preterm child that is randomized to conventional treatment receives Clinoleic (with Vitalipid infant and Soluvit supplementation) according to regular clinical practice and routines as described below.

For all preterm infants the parenteral nutrition with glucose, aminoacids and lipids is introduced within the first 24 hours of life. The intake of lipid emulsion (Clinoleic 20%) is gradually increased during the first days of life with an initial dose of 0.5 g/kg given over 24 hours to a maximum of 2 g/kg/24 h at day 3 to 5 of life. Consequently a preterm infant with a birth weight of 1 kg will receive a maximum of 10 ml lipid emulsion/24 h (2 g/kg). The initial dose of SMOFlipid® will be 0.5 – 1.0 g fat/kg body weight (bw)/day followed by a

successive increase by 0.5 – 1.0 g fat/kg bw/day up to 3.0 g fat/kg bw/day. We will not to exceed a daily dose of 3g fat/kg bw/day, corresponding to 15 mL SMOFlipid®/kg bw/day. The rate of infusion will not exceed 0.125 g fat/kg bw/hour.

This is, according to Brans et al, (Brans, Y.W., Andrew, D.S., Carillo, D.W. et al. Tolerance of fat emulsions in very-low-birth-weight neonates. Am. J. Dis. Child. 1988;142:145-52) is within acceptable levels (i.e 2-3 g/kg/day) for WLBW infants. Enteral feeding with human breast milk is introduced from the first day of life. According to our clinical practice we start with 1-5 ml/kg every third hour depending of maturity and birth weight. The amount of breast milk is slowly and carefully gradually increased during the first 7 to 10 days of life until the infant is fully enteral fed. With increasing enteral amounts the parenteral dose of lipid emulsion is decreased. Some of the most immature infants may have problems to tolerate increased enteral feeding leading to a longer period of parenteral feeding in low doses. In conclusion, feeding WLBW infants according to clinical practice and routine are a regiment with *partial* parenteral nutrition combined with enteral nutrition.

If an infant do not tolerate any enteral feeding (for example gut problems as NEC or during any kind of surgery) the parenteral intake of lipid emulsion may be increased to a maximum of 3g/kg/24 h. The maximum time SMOFlipid® will be administered is to a postmenstrual age of 36 weeks, if the infant still need fatty acid supplementation after this age it will receive fatty acids according to clinical routines. This amount of lipid emulsions is very rare in this patient group and the plasma triglycerides will always be checked although we still are within acceptable levels.

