Sixty (30/30) premature neonates (age 3-7 days, gestational age  $\leq 34$  weeks, birth weights 1000-2500 g) received parenteral nutrition (PN) with either SMOFlipid 20% (study group) or a conventional lipid emulsion (Intralipid 20%, control group) for a minimum of 7 up to 14 days. Lipid supply started at  $0.5 \text{ g} \cdot \text{kg body weight}^{-1} \cdot \text{day}^{-1}$  on day 1 and increased stepwise (by  $0.5 \text{ g}$ ) up to  $2 \text{ g} \cdot \text{kg body weight}^{-1} \cdot \text{day}^{-1}$  on days 4 to 14. Safety and efficacy parameters were assessed on days 0, 8, and 15 if PN was continued.

Adverse events, serum triglycerides, vital signs, local tolerance, and clinical laboratory did not show noticeable group differences, confirming the safety of study treatment. At study end,  $\gamma$ -glutamyl transferase was lower in the study versus the control group ( $107.8 \pm 81.7$  vs  $188.8 \pm 176.7$  IU/L,  $P < 0.05$ ). The relative increase in body weight (day 8 vs baseline) was  $5.0\% \pm 6.5\%$  versus  $5.1\% \pm 6.6\%$  (study vs control, not significant). In the study group, an increase in n-3 FA in red blood cell phospholipids and n-3:n-6 FA ratio was observed.

Plasma  $\alpha$ -tocopherol (study vs control) was increased versus baseline on day 8 ( $26.35 \pm 10.03$  vs  $3.67 \pm 8.06$   $\mu\text{mol/L}$ ,  $P < 0.05$ ) and at study termination ( $26.97 \pm 18.32$  vs  $8.73 \pm 11.41$   $\mu\text{mol/L}$ ,  $P < 0.05$ ).

In conclusion, parenteral infusion of SMOFlipid was safe and well tolerated and showed a potential beneficial influence on cholestasis, n-3 FA, and vitamin E status in premature infants requiring PN.

We now want to study whether supplementation of Omega-3 also protects against ROP in humans.

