### 4 STUDY DESIGN

The study is a Randomised Intervention, Single-Center Study to Determine the Role of Fatty Acids in Serum and Breast Milk in preventing Retinopathy of Prematurity

Subjects who meet all inclusion and none of the exclusion criteria will be enrolled into the study. Upon entry into the study, subjects will be randomized and given a unique subject number.

A randomised intervention study of 45+45 (number based on power analysis regarding up to date ROP frequency, see 5.1 and 11.1) infants without major malformations born with a gestational age less than 28 weeks + 0 days will be performed.

Randomization of the patients to either

- 1) Conventional fatty acid supplementation regime with Clinoleic (with Vitalipid infant and Soluvit supplementation) to the preterm infant

Or

- 2) SMOFlipid® (with Vitalipid infant and Soluvit supplementation), where the quotient of Omega 6:3 is 2.5:1 in order to mimic the physiologic relation of FAs in cord blood from birth, to the preterm infant.

Thus there is one group of infants (n=45) that will receive Omega-3 in the fatty acid supplementation. The time on parenteral nutrition and the amount of fatty acids given will be according to clinical routines. The randomization of the patients will be performed by the controller of the study Randomization will be in blocks with 10 children in each block.

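### Section 6.2 writes a wider titration rule for SMOFlipid than for Clinoleic, so early fat quantity may differ by arm; one shared schedule would remove this

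*Protocol*

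**What the plan says.** Both titration rules stand in Section 6.2, in the subsection on conventional fatty acid supplementation.

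- **Clinoleic.** The initial dose is 0.5 g/kg over 24 hours. It is raised gradually, with no step stated, "to a maximum of 2 g/kg/24 h at day 3 to 5 of life".
- **SMOFlipid.** The start is a range, from 0.5 to 1.0 g/kg/day. The rule for raising it from there is a "successive increase by 0.5 – 1.0 g fat/kg bw/day up to 3.0 g fat/kg bw/day". The next sentence sets 3 g/kg/day as a limit not to be exceeded, and an infusion-rate limit follows.

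Other parts of the Protocol bear on the same question.

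- Section 4 (Study Design) says of both arms that "the amount of fatty acids given will be according to clinical routines".
- The subsection on treated infants in Section 6.2 ties the higher dose to the infant who does not "tolerate any enteral feeding at all for a period leading to an increased dose of fat till at most 3 g/kg".
- The end of Section 6.2 says of any infant who does not tolerate enteral feeding that "the parenteral intake of lipid emulsion may be increased to a maximum of 3g/kg/24 h".
- Sections 6.2 and 8.2 both say that the unit very seldom plans more than 2 g/kg/24 h.
- Sections 6.3 and 11.4 describe blinding for the ROP assessment only.

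**The concern.** The intended contrast is fat type: an omega-6:omega-3 ratio of 2.5:1 for SMOFlipid against 9:1 for Clinoleic (Section 2, choice of study drug). To attribute an effect to that ratio, fat quantity should follow the same rule in both arms. As written, the SMOFlipid arm may start higher, and its schedule sentence runs to 3.0 g/kg/day without the feeding condition that applies elsewhere. A clinician who used that sentence alone would titrate SMOFlipid towards 3.0. One who used the treated-infant subsection would stop at 2 unless enteral feeding failed.

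The staff who set the lipid dose are not stated to be blinded to the emulsion. If they used the extra room in one arm only, quantity would differ together with type. This would blur the reading of ROP (the primary endpoint in Section 11.1). It would also blur fatty acid levels (the first primary objective) and the growth slopes (Section 11.1, secondary endpoints), both plausibly sensitive to the amount of fat.

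**Working it through.** **1. The plan's own conversions.** With a 20% emulsion (0.2 g/mL):
- 2 g/kg ÷ 0.2 = 10 mL/kg, as stated for a 1 kg infant on Clinoleic.
- 3 g/kg ÷ 0.2 = 15 mL/kg, as stated for SMOFlipid.
- 0.125 g/kg/h × 24 h = 3.0 g/kg/day, so the rate limit and the daily limit agree.

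The dose figures are therefore consistent in themselves. The issue is which rule applies to which arm.

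**2. The rules side by side (Section 6.2).**

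| | Clinoleic | SMOFlipid |
|---|---|---|
| Start, g/kg/day | 0.5 | 0.5 to 1.0 |
| Step, g/kg/day | not stated | 0.5 to 1.0 |
| Upper end of the schedule, g/kg/day | 2, at day 3 to 5 | 3.0, no condition in the sentence |
| Limit when enteral feeding is not tolerated, g/kg/day | 3 | 3 |

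**3. Day 1 (firm).** SMOFlipid minus Clinoleic, taking the initial dose as the day-1 dose:
- lowest: 0.5 − 0.5 = 0
- highest: 1.0 − 0.5 = +0.5 g/kg

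**4. Upper end (firm as a conflict of wording).** 3.0 − 2 = 1.0 g/kg/day between the two schedule sentences. At the largest start and step, SMOFlipid would run 1.0, 2.0, 3.0 and reach 3.0 on day 3, when Clinoleic is at 2 at most. This is not a permitted routine difference under the protocol as a whole, because other parts of Section 6.2 reserve 3 g/kg for enteral intolerance.

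**5. Overlap.** The path 0.5, 1.0, 1.5, 2.0 satisfies both rules, with a difference of 0 on every day.

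**6. Why later days are not firm.** Hold both arms to 2 g/kg, use daily SMOFlipid steps, and ignore any reduction for enteral feeds. Totals over days 1 to 5, in g/kg:
- SMOFlipid, slowest (0.5, step 0.5): 0.5 + 1 + 1.5 + 2 + 2 = 7.0
- SMOFlipid, fastest (1.0, step 1.0): 1 + 2 + 2 + 2 + 2 = 9.0
- Clinoleic, linear to day 5: 0.5 + 0.875 + 1.25 + 1.625 + 2 = 6.25
- Clinoleic, linear to day 3: 0.5 + 1.25 + 2 + 2 + 2 = 7.75
- Clinoleic, not linear, also reaching 2 on day 3: 0.5 + 1.5 + 2 + 2 + 2 = 8.0

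With linear Clinoleic paths the difference runs from 7.0 − 7.75 = −0.75 to 9.0 − 6.25 = +2.75. Admitting the non-linear path moves the lower end to 7.0 − 8.0 = −1.0, and moves fastest against fastest from 9.0 − 7.75 = +1.25 to 9.0 − 8.0 = +1.0. Both size and sign depend on a Clinoleic path that the protocol does not give. Section 6.2 also says that "With increasing enteral amounts the parenteral dose of lipid emulsion is decreased", which these totals leave out. They are illustrations only.

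**The case against.** The best defence is that the shared rule already exists. Section 4 refers amounts to clinical routine for both arms, the treated-infant subsection repeats this for all infants, and the enteral-intolerance condition for 3 g/kg is written both for treated infants and for lipid emulsion in general. On this view the SMOFlipid sentences are outer limits for the study product, and staff who follow one routine in both arms break nothing.

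Much of this stands. The protocol as a whole does not license an unconditional rise to 3 g/kg for SMOFlipid, and the absolute limit is the same in both arms. The reading as outer limits is weaker, because the limit has its own sentence directly after the schedule. The 3.0 in the schedule sentence is therefore part of a titration rule, and it conflicts with the conditions elsewhere. The wider start range is not resolved anywhere except by the general reference to routine.

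Three stronger readings are tempting and are not supported.

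- **That SMOFlipid has larger steps.** No Clinoleic step is written. A rise of 0.5, 1.5, 2.0 fits its text and contains a step of 1.0, equal to the largest SMOFlipid step.
- **That the SMOFlipid arm must receive more fat.** The rules overlap, and the illustrative totals include zero and negative differences.
- **That the trial is confounded.** Randomisation still gives a valid comparison of the two regimens, and nothing in the protocol shows that staff would use the extra room.

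Two further slips are editorial only. The synopsis words SMOFlipid as an addition to Clinoleic, but Section 4 makes the two alternatives. The SMOFlipid dosing also stands under the conventional-treatment heading.

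**Conclusion.** The point holds as a minor one about permitted latitude. Section 6.2 gives SMOFlipid a wider start range and a schedule sentence to 3.0 g/kg/day that does not agree with the conditions in the rest of Section 6.2 or with Section 4. The firm size is 0 to +0.5 g/kg on day 1, together with the conflict between 2 and 3 g/kg in the wording. The intake gap on later days cannot be computed from the document, and neither can any effect on ROP or power.

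The consequence is conditional. If staff who know the emulsion used the latitude in one arm, an effect would be harder to attribute to the omega-6:omega-3 ratio. It would remain a valid effect of one regimen against the other. Confidence is high for the difference in wording and does not extend to any consequence in practice.

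**What to change.** State in Section 6.2 that both emulsions follow one schedule:

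- start at 0.5 g/kg/24 h;
- the same stated steps in both arms;
- a routine maximum of 2 g/kg/24 h, reached at day 3 to 5;
- up to 3 g/kg/24 h only when enteral feeding is not tolerated.

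Apart from the common step, every element is already in the protocol, so clinical routine is kept. If steps of 0.5 g/kg are chosen, the path 0.5, 1.0, 1.5, 2.0 fits both present rules. It also matches the schedule that the Introduction describes for a cited SMOFlipid trial, where lipid began at 0.5 g/kg "on day 1 and increased stepwise" to 2 g/kg from day 4. Those infants were older and heavier, so this shows only that one stepwise schedule is workable. With one schedule the permitted day-1 difference becomes 0.5 − 0.5 = 0, and the routine maximum is the same in both arms.

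In the same edit, reword the synopsis so that SMOFlipid replaces Clinoleic, and move the SMOFlipid dosing to the treated-infant subsection. The cost is a few sentences in Section 6.2 and one phrase in the synopsis. Sample size, test, analysis and data collection do not change.

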### **6.3 Blinding**

This is a randomised study with blinded ophthalmologic assessment of ROP stage. Retinal examination will be performed approximately once weekly starting at four to five weeks of age according to a standardized protocol and to clinical screening praxis. The assessing, evaluation of ROP stage 3 or more, independent from the study, pediatric ophthalmologists will be unaware which infants are participating in the study.

## **7 STUDY CONDUCT**

### **7.1 Ethics and Regulatory Considerations**

This study will be conducted in accordance with current Good Clinical Practices (GCPs) and International Conference on Harmonization (ICH) recommendations, as well as all applicable local, state, and federal regulations and guidelines regarding the conduct of clinical trials.

### **7.2 Independent Ethics Committee**

The protocol, informed consent form, and other written subject information must be submitted to the “Regionala Etikprövningsnämnden i Göteborg” (REG) and their written unconditional approval must be obtained prior to commencement of the study.

Verification of unconditional approval from REG of the protocol and the approved informed consent form will be forwarded to Kabi Fresenius, the manufacturer of the study medication, prior to shipment of study medication supplies to the site.

### **7.3 Informed Consent/Assent Form**

Informed consent by the parents/guardians for each subject will be obtained before initiating any study procedures. Both parents/guardians will have to sign the informed consent. Informed consent should be obtained as soon as possible after birth and no later than 24 hours after birth. One copy of the signed and personally dated informed consent must be given to each parent/guardian and one signed and personally dated copy must be retained in the investigator's trial records. The "Declaration of Helsinki" recommends that consent be obtained from each potential subject or parents/guardians in biomedical research trials after the physician has explained to the individual the purpose, methods, anticipated benefits, and potential hazards of the trial and discomfort it may entail.

Potential subject's parents/guardians should also be informed of their right not to participate or to withdraw from the study at any time. If the individual is in a dependent relationship to the physician or gives consent under duress, an independent physician should obtain the informed consent. If the individual is legally incompetent (i.e., a minor or mentally incompetent), informed consent must be obtained from the parent, legal guardian, or legal representative in accordance with the law in Sweden. See Appendix No. III for the "Declaration of Helsinki".

If a protocol amendment substantially alters the study design or there is an increase of a potential risk to the subject:

- the informed consent form or subject information sheet must be revised and submitted to the MPA and REG for review and approval; and
- the approved revised form must be signed by parents to subject currently enrolled in the study; or
- the new form must be used to obtain consent from new parents prior to enrollment into the study.

